### Statistical Analysis

In our pilot study [33], we found that approximately 10% of sexually active AYAs reported being tested for HIV in the past 4-6 months. A sample of approximately 300 subjects (150 per arm) would achieve >80% power to detect a moderate effect corresponding to a difference of at least 13 percentage points (equivalent to a relative risk of 2.3 assuming a 10% prevalence of HIV testing in the past 4-6 months in the control group) in HIV testing between the intervention and control groups after 6 months using a two-sided test at a 5% significance level and assuming a 16% attrition rate after 6 months. All data will be inspected for inaccurate input (eg, out-of-range values, implausible means, and variation). We will first summarize the outcome measures descriptively overall and within each intervention arm at each time point. We will make every effort to obtain all data. Any patterns of missingness will be investigated and reported. Sensitivity analyses, including rerunning analyses with imputed values for missing data, will be conducted to assess the impact of missingness on the study findings.

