All primary analyses will be conducted using an intent-to-treat approach. The primary analysis will focus on differences between the treatment and control groups at the 6-month follow-up visit using a chi-square test for independence (the outcome will be taken as having had an affirmative response on the outcome measure during the 6-month study period). We will also investigate the differences between the rates of HIV testing in the treatment and control groups, stratifying by age (13-17 years vs 18-24 years) and sexual orientation (LGBTQ+ vs heterosexual identity). We will perform a longitudinal analysis on the repeated measures from each subject using logistic mixed effects models with a subject-specific random intercept. In each model, we will include time as a 4-level categorical predictor (with baseline serving as the reference level) as well as a treatment indicator and time-by-treatment interaction. We will jointly test the interaction coefficients to determine if the effect of treatment varies over time. If the effect is found to vary over time, we will test the intervention effect at each time point and characterize the difference between the treatment and control groups using risk differences and their corresponding 95% CIs. If no evidence of a time-by-treatment interaction is present, we will refit the logistic model without the interaction terms and provide the overall intervention effect and its corresponding 95% CI.

Furthermore, we will provide a descriptive analysis of each secondary outcome overall and within each intervention arm at each time point. Secondary outcomes will also be compared between the treatment and control groups using one-tailed *t* tests for continuous measures and chi-square tests for categorical measures. The corresponding group differences (in mean scores or proportions) and their 95% CIs will be reported. Within the intervention group, we will investigate game use changes over time and whether there exists a dose-response relationship between various game use indicators (eg, amount of time playing the game) and the various survey responses, including HIV testing, intent to test for HIV, PrEP uptake, and intent to seek PrEP as well as the other secondary outcomes. Qualitative data from IDIs will be transcribed and involve thematic coding using Atlas.ti version 7.0 to identify themes regarding intervention delivery and acceptability.

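### Continuous secondary outcomes get one-tailed t tests without a stated reason, out of line with the chi-square tests and 95% CIs beside them and with the protocol's only stated level, two-sided 5%

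*Protocol article*

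**What the plan says.** All the relevant text is in the Statistical Analysis section of the protocol article.

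- **Secondary outcomes, test:** "Secondary outcomes will also be compared between the treatment and control groups using one-tailed" *t* "tests for continuous measures and chi-square tests for categorical measures".
- **Secondary outcomes, estimates:** "The corresponding group differences (in mean scores or proportions) and their 95% CIs will be reported".
- **Primary outcome, test:** group difference in HIV testing at 6 months, "using a chi-square test for independence".
- **Level:** the power statement for HIV testing is made "using a two-sided test at a 5% significance level". No other significance level appears in the article.

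The section gives no level, direction or reason for the one-tailed tests. The Theoretical Framework for Intervention section does say what the investigators expect: higher risk perception, more HIV and PrEP knowledge, and better self-efficacy. It does not present those expectations as grounds for one-tailed testing.

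**The concern.** Two standards of evidence sit in one sentence. Whether a secondary outcome faces a directional or a non-directional test depends only on how it is scored. Intent to test, which the Secondary Outcomes section dichotomizes, goes to chi-square. A knowledge score analysed as a mean goes to a one-tailed t test.

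The tests also may not match the intervals reported with them. A conventional 95% CI corresponds to a two-sided 5% test, so a one-tailed 5% test can be significant when the interval includes zero.

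The test also ignores the unfavourable side. The control arm is an active app with HIV and PrEP information, a link to the risk estimator, and testing and PrEP locators (Control Condition section). The game could therefore do worse than the control on some scale, and a one-tailed test could not declare it. Knowledge and risk behaviors are part of the article's stated efficacy question, so these p-values are likely to support claims.

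**Working it through.** **Inputs from the Statistical Analysis section.** 150 per arm; 16% attrition at 6 months; 10% control rate; 13-point difference, hence 23% in the intervention arm; two-sided 5%; 80% power.

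**Analysed sample.** 150 × (1 − 0.16) = 126 per arm, so a two-sample t test has 2 × 126 − 2 = 250 degrees of freedom.

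**Step 1: is the planning standard really two-sided?** The article claims that "A sample of approximately 300 subjects (150 per arm) would achieve >80% power to detect a moderate effect". With p̄ = (0.10 + 0.23)/2 = 0.165:

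- Null SE = √(2 × 0.165 × 0.835/126) = 0.0468.
- Alternative SE = √((0.10 × 0.90 + 0.23 × 0.77)/126) = 0.0460.
- Power, pooled null variance = Φ((0.13 − 1.96 × 0.0468)/0.0460) = 79.8%.
- Power, unpooled variance = Φ(0.13/0.0460 − 1.96) = 80.6%.
- The one-sided version gives 87.6%.

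The stated power is reproduced, within rounding, by the two-sided calculation. The trial was planned to a two-sided 5% standard.

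**Step 2: critical values for a continuous outcome, 250 df.**

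| Test | Critical t | Chance of a false claim of benefit |
|---|---|---|
| One-tailed 5% | 1.651 | 5.0% |
| Two-sided 5% | 1.969 | 2.5% |
| One-tailed 2.5% | 1.969 | 2.5% |

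The doubling appears only in the first row, and the article does not state the one-tailed level.

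**Step 3: conflict between p-value and CI, if one-tailed 5% is used.** For t between 1.651 and 1.969 the test rejects while the two-sided 95% CI includes zero. For example, t = 1.80 gives one-tailed p = 0.037 and two-sided p = 0.073.

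- With no true effect, the conflict has probability 5.0% − 2.5% = 2.5% per outcome.
- With a true benefit of 0.2 SD (an illustrative value), rejection rates from the noncentral t are 47.5% one-tailed and 35.2% two-sided. About 12% of trials would then show the conflict. These are not false positives, but the two reported results would point different ways.

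**Step 4: unfavourable effects.** For a true harm of 0.3 SD (also illustrative), the one-tailed 5% test rejects with probability about 0.00003. A two-sided test detects the harm 66% of the time. The two-sided 95% CI excludes zero on the harmful side equally often, because it is the same calculation.

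**Step 5: price of two-sided testing.** Effect detectable with 80% power, in SD units, is (z for the level + z for the power) × √(2/126):

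- One-tailed 5%: (1.645 + 0.842) × 0.1260 = 0.313.
- Two-sided 5%: (1.960 + 0.842) × 0.1260 = 0.353.

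**The case against.** The defence has four parts, and each narrows the point.

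1. **A reader might infer that false claims of benefit necessarily double.** The article does not support that. It gives no level for the one-tailed tests, and its 5% belongs to the primary outcome's power statement. At one-tailed 2.5% there is no doubling and no conflict with the CI. What remains is that 5% is the only level stated, so it is the natural reading. Even then, total type I error per outcome is 5%, the same as for a two-sided 5% test; it has all moved to the benefit side.

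2. **A reader might infer that harm could never be shown.** That is wrong. The article promises 95% CIs and descriptive summaries by arm at each time point. Read as ordinary two-sided intervals, those CIs can exclude zero on the harmful side. The blindness belongs to the test and its p-value, not to the whole report.

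3. **A reader might infer that no direction is given anywhere.** The Theoretical Framework section gives one for risk perception, knowledge and self-efficacy, so the tail can be inferred for those. Other measures listed under secondary outcomes, such as CDC risk estimator scores and alcohol and drug use in Table 1, have no stated direction. Whether these will be analysed as continuous is not said. An expected direction is also not, by itself, a reason to disregard the other one.

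4. **The reach is limited.** Intent to test is dichotomized, and PrEP uptake is naturally binary. Both would go to chi-square. The one-tailed test mainly touches scale scores.

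A full analysis plan may state the level, so its absence from an article is not the complaint. The complaint is that the article does specify one tail, beside two-sided companions and without a reason.

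**Conclusion.** The point holds in limited form. The one-tailed t tests do not match the non-directional chi-square tests in the same sentence or the two-sided 5% standard to which the trial was planned. At 5% they would not match the reported 95% CIs either.

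The false-benefit and CI-conflict figures rest on three assumptions: a one-tailed level of 5%; 126 analysed per arm, which applies the 16% attrition equally to both arms; and 95% CIs of the usual two-sided kind. The t test's inability to declare an unfavourable effect needs none of these.

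The primary outcome, its test and the sample size are unaffected. This should be corrected because it changes which continuous secondary results count as significant, but it does not put the trial's main conclusion at risk.

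**What to change.** In the secondary-outcomes paragraph of the Statistical Analysis section, replace *one-tailed t tests* with *two-sided t tests at the 5% level*. The t tests then agree with the chi-square tests, the 95% CIs and the planning level.

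The cost is a small loss of sensitivity to benefit: the effect detectable with 80% power rises from about 0.31 SD to about 0.35 SD. No change to sample size or data collection is needed. The article describes the study as still in its formative phase, so the change can be made before any trial outcome data exist.

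If the investigators prefer to keep one tail, they should state the level, the direction for each measure and the reason. A one-tailed level of 2.5% would restore the benefit-side error and agreement with the CI, but the test would still be unable to declare an unfavourable effect.

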### Incentives

For their participation in the formative focus groups, AYAs will receive a US $30 gift card and an additional US $10 gift card for a peer recruited who participates in the focus group. For their participation in the pilot test, AYAs will receive US $80 gift cards (US $20 for the baseline survey, US $30 for the 1-month survey, and US $30 for the IDI). For their participation in the RCT, AYAs will receive up to US $150 in gift cards (US $30 for the baseline survey, US $25 for the 1-month survey, US $25 for the 3-month survey, US$40 for the 6-month surveys, and US $30 for the IDI).

### Ethical Considerations

To protect participants from potential loss of confidentiality, the following measures will be taken: informed consent and assent will be required for participation in the focus groups, pilot testing, and intervention. Each study participant will be assigned a pseudonym to participate in the focus groups, and interviews and surveys will be labeled with a study ID. Participants will be informed that individual results will not be shared, and only aggregate results will be disclosed at study completion. Summary statistical data stratified by age, race, or other categories may be released. However, if the total information will allow identification of the exact person or persons the information will not be released.

All study-related materials will only be accessible to the research staff. All data collection will take place with HIPAA-compliant software (ie, WebEx and REDCap). All study personnel have completed training and received certification in Human Subjects Research Protection (Collaborative Institutional Training Initiative Program) and HIPAA regulations and will continue to renew this training in compliance with institutional review board policies. We will adapt measures successful in other studies to reduce the risk of potential breaches by using passwords, not sending any sensitive information, and eliciting AYAs’ preferred method of communication and receipt of study information (eg, surveys and incentives).

## Results

The study was funded on April 2, 2020. The protocol has been reviewed and approved by the George Washington Institutional Review Board (NCR191708) on February 5, 2020 and was registered on ClinicalTrials.gov (NCT04917575). Data collection for the formative phase is projected to begin in June 2021.

## Discussion

### Review

The life-simulation gaming intervention aims to increase HIV testing and PrEP access among AYAs by reducing individual and structural barriers. Through digital content aligned with SCT and the HBM, the intervention attempts to positively influence youth self-efficacy, risk perceptions, and knowledge of HIV prevention as well as influence AYAs’ social support.

### Limitations and Anticipated Challenges

There are several potential challenges to the success of our trial. First, if it is determined that AYAs in the formative focus groups do not like the proposed enhancements, we will modify the game accordingly. Second, for all 3 phases, we plan to intentionally recruit AYAs who are not regular clinic attendees and rely primarily on social media recruitment. If this proves challenging, we will consider expanding recruitment to local community-based organizations that are not HIV focused and consider recruiting from after-school programs or events geared toward AYAs. Third, although web-based recruitment is ideal to identify our population of interest, there is a risk of fraud, and we plan to have staff verify the eligibility of potential participants. Finally, AYAs’ gaming preferences change far faster than the pace of research. Avatar clothes and other in-game items may no longer be popular during the game’s release. The software architecture is designed to be modular and flexible to allow many elements to be altered both before and after release. To ensure adequate game content to keep AYAs engaged during the study period, as per industry standards, we will build in frequent releases of new game content.

### Conclusions

As the number of new HIV infections among AYA continues to grow, innovative methods to scale up HIV prevention for this population are required. The results of this study will be useful for understanding the extent to which a digital game can increase HIV testing and PrEP access among AYAs. If effective, we will work with the local health departments, health clinics, and school-based clinics to make the game available to their students and patients. We will also look into making the game and locators relevant and available to AYAs living in areas of the United States with some of the highest rates of HIV infection, such as the Southern United States.

## Appendix

Multimedia Appendix 1 Peer-review report by the Center for Scientific Review Special Emphasis Panel, Small Business: Disease Prevention and Management, Risk Reduction and Health Behavior Change (National Institutes of Health).

## Abbreviations

AYA: adolescents and young adults
HBM: health belief model
HIPAA: Health Insurance Portability and Accountability Act
IDI: in-depth interview
LGBTQ+: lesbian, gay, bisexual, transgender, queer or questioning, and others
PrEP: pre-exposure prophylaxis
RCT: randomized controlled trial
REDCap: Research Electronic Data Capture
SCT: social cognitive theory
YMSM: young men who have sex with men
